### Study Timeline

The study will take place over 4-5 months for each participant, and the total study duration is expected to last 2.5 years. Consenting participants will be enrolled, randomized, and administered a baseline assessment on the first day. They will be scheduled to receive the Just Do You core component within 1 week of completing the baseline. They will receive each subsequent component within 1 week of the previous component based on their experimental condition (Figure 2). After completing the intervention, participants will be administered the posttest assessment, which includes the study outcomes and acceptability measures. Participants will be administered the final assessment 3 months after the baseline, and the research staff will receive a report from the study site documenting each date a treatment service was received by the participant over the study period.

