### Randomization

Upon enrollment in the study, participants will be assigned to an experimental condition using a randomization plan programmed into a database on the REDCap (Research Electronic Data Capture) platform [81]. The program will assign participants using block randomization to maximize balance across conditions (ie, random assignment to 1 of 8 conditions per block). Condition assignments will be unblinded.

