### Intervention

The intervention period for each participant will last from 1 to 5 weeks, depending on the experimental condition. The conditions have a maximum of 5 sessions, delivered once per week, and sessions last for up to 1.5 hours (refer to content in Table 2). Following a baseline assessment, the core intervention will be delivered for all participants, and additional components will be delivered subsequently in the following weeks. In addition, participants are expected to attend all appointments for mental health treatment at the study site. All intervention components will be delivered by a mental health clinician and a professional peer specialist employed by the study site. The principal investigator will provide initial and ongoing training to the interventionists on the manualized intervention components and reporting procedures for adverse events throughout the study.

**Table 2 table2:** Content and duration of components.

Component	Number and duration of sessions	Topics and activities
Just Do You	1 Session 60 minutes	Guiding principles of recovery Recovery Role Model personal narrative Videos of celebrity service users Personal goals related to recovery Characteristics of a trustworthy professional Introduction to clinic services
A: Cultural identity	1 Session 60 minutes	Feeling seen and heard Introduction to creative arts therapy techniques Cultural identity art activity Recovery Role Model personal narrative
B: Future self	2 Sessions 60 & 30 minutes	Session 1 Overcoming challenges and finding hope Introduction to creative arts therapy techniques Mental health resilience in music and videos Strengths and inspiration of art activity Recovery Role Model personal narrative Introduce guidelines for photo activity Session 2 Brief check-in after completing the photo activity
C: Understanding environments	1 Session 60 minutes	Overcoming barriers in the environment Introduction to creative arts therapy techniques Map of your environment art activity Recovery Role Model introduces services/strategies for addressing barriers to engagement

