### Assessment Procedures

Assessments of engagement will occur at baseline, posttest (after intervention completion), and 3-month follow-up. At each assessment, participants will report on involvement in their treatment, and their perceptions of stigma, benefits, trust and rapport with providers, hopefulness, and the difficulty associated with treatment engagement. In-depth acceptability interviews will be conducted at posttest with 40 participants purposively sampled from each experimental condition. Acceptability interviews will be focused on experiences with intervention components, aspects of implementation, and any factors that promoted or impeded intervention adherence. Each assessment is expected to last for 1 hour.

Screening, consent, and assessment interviews with participants will be administered by the principal investigator or another trained member of the research team and will take place in person at the study site or via encrypted videoconferencing. All staff involved in data collection will be trained on the assessments by the principal investigator, and all research staff will complete training on informed consent, good clinical practices, and all safety and reporting protocols as certified by New York University’s institutional review board (IRB).

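### Open assignment precedes the same-day baseline interview, so baseline engagement and mediator scores can be affected by knowledge of the assigned condition

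*Protocol article*

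**What the plan says.** Two sections of the protocol article describe the order of steps, and they agree.

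- Study Timeline: "Consenting participants will be enrolled, randomized, and administered a baseline assessment on the first day".
- Randomization: "Upon enrollment in the study, participants will be assigned to an experimental condition using a randomization plan programmed into a database". The same section states "Condition assignments will be unblinded".

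The Intervention section places the baseline only relative to treatment: "Following a baseline assessment, the core intervention will be delivered for all participants". That does not put it before randomization.

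On how the baseline is collected, Assessment Procedures says that "assessment interviews with participants will be administered by the principal investigator or another trained member of the research team", and "At each assessment, participants will report on involvement in their treatment, and their perceptions of stigma, benefits, trust and rapport with providers". The same list also covers how hopeful participants feel and how hard they find it to engage. The Measures section adds that the targeted mediators are self-reported at every timepoint, and that service contacts come from medical records beginning one month before baseline.

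The Data Analysis section names two outcomes for the factorial ANOVA: mean change in contacts and level of engagement at 3 months. It also plans to look at mediators, and says the results will be read as an overall pattern of changes rather than through hypothesis tests.

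**The concern.** A baseline score serves as a reference only if the assignment cannot have influenced it. Here the interview follows an open assignment. A participant who has just learned that a session on their future self will or will not follow may answer differently about hope. An interviewer who knows the condition may also prompt or record differently. Hope, self-efficacy and perceived provider competency are what the three components are meant to move, so the exposed scores are the relevant ones.

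If the included and excluded levels of a factor already differ at baseline for this reason, subtracting or adjusting for baseline carries that difference into the estimated component effect. A baseline raised by the assignment hides benefit, and a lowered one creates it. The pilot's effect estimates are to be read by strength and direction, and both can be distorted. Some reporting bias after treatment is hard to avoid in an unblinded behavioral trial, but this part of it is avoidable.

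**Working it through.** **1. Order of steps.** Study Timeline lists enrollment, randomization and baseline in that sequence. Read alone, the sentence could be an unordered list of day-one events. The Randomization section ties assignment to enrollment, which supports the sequence as written. No section puts the baseline first, delays disclosure or masks the assessor.

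**2. Which outcomes are exposed.**

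| Quantity | Source | Exposed? |
|---|---|---|
| Change in service contacts | Medical records, from one month before baseline | No |
| 3-month engagement level, unadjusted | Self-report at follow-up only | No, baseline not used |
| Engagement as a change or baseline-adjusted | Self-report | Yes |
| Mediators as a change or baseline-adjusted | Self-report | Yes |

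**3. Does the plan's own power figure use the baseline?** Inputs from Data Analysis: N = 80, d = 0.50, correlation 0.6, α = .05, stated power 79%. Each main effect compares 40 with 40 (Table 1). Two-sided testing is assumed.

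- Baseline-adjusted: residual SD = √(1 − 0.6²) = 0.8. Power is 79.8% (normal) or 78.7–78.8% (noncentral t). This matches the stated 79%.
- Unadjusted: SD = 1. Power is 60.9% (normal) or 59.8% (t).
- Change score: SD = √(2 × (1 − 0.6)) = 0.894. Power is 70.5% (normal) or 69.5% (t).

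A one-sided change-score test gives 79.8% (t), and it too uses the baseline. The stated power therefore appears to rest on the baseline score. That the 0.6 is a baseline to follow-up correlation is inferred from this match; the article does not say so.

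**4. Size of the bias.** Let b be the shift in mean baseline, in SD units, that knowledge of assignment causes in the included level relative to the excluded level, with follow-up unaffected. With equal SDs the adjustment slope equals the correlation, 0.6.

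- Change score: estimate = d − b
- Baseline-adjusted: estimate = d − 0.6b

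With true d = 0.50:

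| Assumed b | Change score | Baseline-adjusted |
|---|---|---|
| −0.2 | 0.50 + 0.20 = 0.70 | 0.50 + 0.12 = 0.62 |
| +0.1 | 0.50 − 0.10 = 0.40 | 0.50 − 0.06 = 0.44 |
| +0.2 | 0.50 − 0.20 = 0.30 | 0.50 − 0.12 = 0.38 |
| +0.3 | 0.50 − 0.30 = 0.20 | 0.50 − 0.18 = 0.32 |

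With no true effect, a shift of 0.2 SD produces an apparent effect of 0.20 (change score) or 0.12 (adjusted). The standard error with 40 per level is 0.894 × √(2/40) = 0.20 for the change score and 0.8 × √(2/40) = 0.18 for the adjusted estimate. The spurious effect is thus about one standard error in the first case and about two thirds of one (0.12/0.18) in the second.

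**The case against.** The best defense is that the consequence is conditional and the trial is a pilot.

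- **Time of disclosure is not stated.** Unblinded does not say when the participant or interviewer learns the condition, and the timeline figure is not shown. This stands: the bias is possible, not demonstrated.
- **The named outcomes may escape it.** Contacts come from records, and engagement is named as a 3-month level. This also stands, and it limits the point to analyses that use the self-reported baseline.
- **The shift has no anchor.** Everyone receives Just Do You, and each main effect averages over the other two components, so the levels differ by one component of one or two sessions. The contrast of no extra components with all three is not the planned comparison. The table above therefore shows sensitivity and is not a forecast.
- **The aims are feasibility and acceptability.** Those benchmarks do not use baseline scores, and effects are exploratory. This lowers the stakes, but a pattern of changes read by direction and strength still depends on a sound baseline.

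A reader might infer two stronger points. One is that participants who leave between assignment and interview are lost to the intention-to-treat analysis. Their service contacts may still be available from clinic records, the interval is within one day, and nothing suggests losses are expected there. The other is that staff can predict assignments, from "ie, random assignment to 1 of 8 conditions per block". The article gives no explicit block size and does not say that enrolling staff see the allocation list, so predictability is not established.

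**Conclusion.** The point holds for self-reported engagement and mediators wherever their baseline is used. As written, the plan randomizes openly before the baseline interview and states no safeguard. The bias would be b for change scores and about 0.6b for baseline-adjusted estimates. The first follows directly from subtraction; the second rests on the inferred meaning of the 0.6. The size of b is unknown. At an assumed 0.2 SD, a true effect of 0.50 would read as 0.30 or 0.38.

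It would be wrong to conclude that the trial's main results are compromised. Change in contacts, the unadjusted 3-month engagement level, and the feasibility and acceptability findings are not affected by this route. It is a limited, avoidable weakness that is cheap to correct while recruitment, planned through December 2026, continues.

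**What to change.** For remaining participants, keep the single first-day visit but change the order: consent, complete and lock the baseline record, then trigger the REDCap randomization. If the order cannot be changed, withhold the assignment from both participant and interviewer until the baseline is complete. State the chosen order in the Randomization and Study Timeline sections so that they agree explicitly.

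Record which participants were enrolled before and after the change. Compare component effects on the self-reported measures between the two groups as a sensitivity analysis, and report the unadjusted 3-month engagement level alongside any baseline-adjusted result.

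The cost is a minor amendment during recruitment, which the article says goes to the IRB and is reported on the registry, and two cohorts whose baselines were taken under different conditions. N = 80 and the stated 79% power do not change, and no visit is added.

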Engagement in treatment will be measured using 8 items from the Client Engagement in Child Protective Services Scale involvement or buy-in subscale [83]. Responses are on a 5-point Likert scale. An example item is “I am not just going through the motions. I’m really involved in working with providers.” The range for the scale is 8 to 40, with higher scores indicating higher levels of engagement. This scale has demonstrated acceptable reliability with the study target population (=.82) [51,83]. Service usage will be measured at a 3-month follow-up by participant medical records. The total number of contacts each participant makes with the treatment program, and the dates for all contacts, starting 1 month before baseline through 3-month follow-up, will be collected to assess change in service use over the study period. Demographic information will be collected at baseline, and targeted mediators and mental health symptoms will be collected by self-report measures at all timepoints. Study measures have been extensively tested by the research team [84] and previous studies with REM populations, young adults, and individuals living with SMI. All have been found to have good psychometric properties. Can be found in Multimedia Appendix 2: Baseline assessment measures for a full list of the study measures collected during the baseline assessment.

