To assess treatment engagement outcomes, exploratory analyses will examine the distributions of all variables, identify outliers, and calculate descriptive statistics for each assessment timepoint, and with respect to the 3 components. We will use an intent-to-treat approach for the analysis. Factorial ANOVA using effect coding will be used to estimate the main effects and interactions between factors (ie, components) on the mean change in number of contacts with treatment services and the level of engagement at 3-month follow-up. Each intervention component will be assigned a value of +1 or –1 depending on whether it was included or excluded from the experimental condition (ie, yes or no). In addition, we will explore evidence of effects on mediators at posttest and 3-month outcomes. Analyses will rely on an examination of the overall pattern of changes (eg, strength and change in the intended direction) instead of hypothesis testing. The sample size of 80 is sufficient for the planned analyses and provides 79% power to detect main effects, corresponding to a correlation of 0.6 and a medium effect size (*d*=0.50), given α=.05.

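### The posttest is tied to completing the intervention, with no posttest stated for early stoppers, so acceptability and posttest mediator data risk coming from completers only

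*Protocol article*

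**What the plan says.** Two sections define the posttest by completion. The Study Timeline states: "After completing the intervention, participants will be administered the posttest assessment, which includes the study outcomes and acceptability measures". Assessment Procedures states: "Assessments of engagement will occur at baseline, posttest (after intervention completion), and 3-month follow-up". The final assessment has a different anchor: "Participants will be administered the final assessment 3 months after the baseline".

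The length of the intervention depends on assignment. The Intervention section says "The intervention period for each participant will last from 1 to 5 weeks, depending on the experimental condition" and "The conditions have a maximum of 5 sessions, delivered once per week". Table 2 gives one session each for the core program, A and C, and two for B.

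The acceptability questionnaire is placed at posttest (Study Timeline), as are the 40 in-depth interviews (Assessment Procedures), which are also meant to explore what helped or hindered adherence. Under Measures, "targeted mediators and mental health symptoms will be collected by self-report measures at all timepoints", and Data Analysis includes mediators at posttest. Acceptability is judged by a mean rating above the scale midpoint together with positive interview themes. In the paragraph on engagement outcomes, Data Analysis adds: "We will use an intent-to-treat approach for the analysis".

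For dropouts, Measures provides only for follow-up contact to learn their reasons. No section gives a posttest time for a participant who stops before the last assigned session, and no section says that such a participant is left out.

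**The concern.** A measurement triggered by completion depends on behaviour after randomization. Two consequences follow if the rule is applied as written.

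First, people who stop early may be those who found the sessions least acceptable. If they give no rating and no interview, both parts of the acceptability judgement lean towards those who stayed. The interviews would also miss the people best placed to say what hindered adherence. Acceptability belongs to the first listed goal of the pilot, and Data Analysis uses it to decide which elements are modified or removed.

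Second, participants assigned more components have more to complete before they qualify for the posttest. Missing posttest mediator scores would then be related to the factors being compared.

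A separate matter needs no assumption about dropout. Even with full completion, the planned time from baseline to posttest differs between the two levels of every factor, so posttest mediator contrasts also compare different lengths of time in routine care.

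**Working it through.** **Planned time to posttest.** Sessions per condition = 1 + A + 2B + C, with each component coded 1 if included and 0 if not (Tables 1 and 2), at one session per week. Conditions 1 to 8 give 1, 2, 3, 4, 2, 3, 4 and 5. This reproduces the article's range of 1 to 5 weeks. Averages over the four conditions at each level:

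| Factor | Included | Excluded | Difference |
|---|---|---|---|
| A | (2+3+4+5)/4 = 3.5 | (1+2+3+4)/4 = 2.5 | 1 week |
| B | (3+4+4+5)/4 = 4.0 | (1+2+2+3)/4 = 2.0 | 2 weeks |
| C | (2+4+3+5)/4 = 3.5 | (1+3+2+4)/4 = 2.5 | 1 week |

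**How many would reach posttest if completion is required.** The article gives no figure for this, so what follows is an illustration. Assume each assigned component is completed independently with probability q. The number of components including the core is 1, 2, 2, 3, 2, 3, 3 and 4 in conditions 1 to 8. With 10 participants per condition, the expected number is 10 × (q + 3q² + 3q³ + q⁴).

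| q (assumed) | Condition 1 | Condition 8 | Expected of 80 | With vs without any one component |
|---|---|---|---|---|
| 0.95 | 95% | 81% | 70.4 (88%) | 86% vs 90% |
| 0.90 | 90% | 66% | 61.7 (77%) | 73% vs 81% |
| 0.85 | 85% | 52% | 53.8 (67%) | 62% vs 73% |

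For q = 0.85: 10 × (0.850 + 2.168 + 1.842 + 0.522) = 53.8. The value 0.85 borrows the article's component-completion benchmark as a per-component rate. If the benchmark instead means that 85% of participants finish everything assigned, the number is 0.85 × 80 = 68, which lies inside the same range. At q = 0.85 the overall 67% would fall below the article's own 75% benchmark for completed assessments; at 0.90 it would not.

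**Effect on the acceptability criterion.** The scale runs from 9 to 45, so the midpoint is (9 + 45)/2 = 27. Let a fraction f have no rating and let completers average m. The all-participant mean is 27 or below when the unrated group would have averaged at most (27 − (1 − f)m)/f.

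- f = 0.25, m = 28: (27 − 21)/0.25 = 24.
- f = 0.25, m = 30: (27 − 22.5)/0.25 = 18.
- f = 0.15, m = 28: (27 − 23.8)/0.15 = 21.3.
- f = 0.15, m = 30: (27 − 25.5)/0.15 = 10, close to the scale minimum.

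The values of f and m are assumed. The criterion could be met only because ratings are missing if completers score just above the midpoint. If they score well above it and few are missing, the conclusion would hardly change.

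**The case against.** The strongest reply is that the two sentences give only the order of visits. A reader might infer that the plan excludes early stoppers, that acceptability is therefore biased upward, and that the posttest mediator analysis is not intention-to-treat. The documents do not establish any of these. No section excludes early stoppers. Intent-to-treat is stated, assessment and component completion have separate benchmarks, adherence is counted as the number of components completed, tracking and reminders cover all participants, and the purposive interviews ask about obstacles to adherence. A journal article may also leave the handling of early stoppers to the full protocol.

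This removes any claim of established bias or of a known number missing. It does not remove the risk. The article is not silent on when the posttest occurs: it names completion twice. An intent-to-treat label cannot supply scores that were never collected, and it appears in the paragraph on engagement outcomes, not in the one on acceptability. Reasons for dropout and interventionist feedback are useful, but neither is a rating or an interview.

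On timing, the reply is stronger. Assessing soon after the last session is a reasonable way to capture proximal change in mediators. The analyses look at patterns and not at hypothesis tests, and the size of any bias from 1 or 2 extra weeks of usual care is not shown. A single posttest at, say, 6 weeks would equalize time since baseline but leave about 6 − 1 = 5 weeks since the last session in condition 1 against 6 − 5 = 1 week in condition 8. That is a trade-off, so the varying posttest time cannot be called a plain error.

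**Conclusion.** The point holds as a risk created by a stated rule. Read literally, the posttest is reached only by completing the intervention, and everything described for acceptability ratings and interviews hangs on it. The possible loss covers the acceptability data and the posttest engagement, mediator and symptom scores. Under an assumed, independent completion of 85% to 95% per component, about 54 to 70 of 80 would be assessed at posttest, with coverage 4 to 11 percentage points lower where a given component is included (85.8% vs 90.3% at 0.95; 61.8% vs 72.7% at 0.85). If early stoppers are in fact assessed, loss from this source is zero.

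The differences in planned posttest time (A and C 1 week, B 2 weeks) follow directly from the tables and call for caution in reading posttest mediator contrasts.

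Engagement, service contacts and mediators at 3 months do not depend on completion. That they also share a common time from baseline rests on the baseline anchor in the Study Timeline. The same section gives 4 to 5 months of participation per person, which should be reconciled with a final assessment at 3 months.

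**What to change.** 1. State that every randomized participant is given the posttest whether or not all sessions were completed, with early stoppers assessed at the scheduled end of their assigned condition.
2. Give the acceptability questionnaire after the last attended session or on stopping, and report ratings separately for completers and early stoppers.
3. Include early stoppers explicitly among the 40 purposively sampled interviews.
4. Rest component comparisons on mediators mainly on the baseline-anchored 3-month assessment, and report posttest contrasts with the planned timing differences beside them. One fixed posttest time for all is an option, at the cost of unequal time since the last session.

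The cost is a small amendment to the scheduling wording and some extra effort to reach people who have stopped attending. The number of planned assessments per participant does not change, and the contact details and reminders already planned for all participants can be used.
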